## b) Rationale

Abdominal pain is one of the most common reasons for children and adolescents to seek care in the ED. About 5%-10% of all pediatric ED visits are for abdominal pain, and appendicitis is ultimately diagnosed in up to 10% of these children. Appendicitis is the most common surgical emergency in pediatrics. The lifetime risk of appendicitis is 8.6% for males and 6.7% for females. When evaluating pediatric patients with acute abdominal pain, ED physicians often consider surgical conditions, such as ovarian torsion or cholecystitis, in addition to appendicitis; however, these conditions are uncommon in children. In a recent multicenter study of more than 2,500 pediatric patients (3-18 years old) presenting to an ED with <96 hours of abdominal pain, 39% had appendicitis, while only 1.1% of patients had a surgical condition other than appendicitis.

Despite the high incidence, diagnosing appendicitis remains challenging. The clinical presentation of non-surgical conditions causing acute abdominal pain (e.g., mesenteric adenitis, acute gastroenteritis) often mimics that of appendicitis. In addition, children may have difficulty communicating their complaints. Up to 40% of children with appendicitis are misdiagnosed on initial presentation, leading to delays in treatment and increased morbidity and mortality. There is also considerable variability in the ED evaluation of children with suspected appendicitis. A recent survey of 40 US children's hospitals demonstrated that, among children with appendicitis, CT use ranged from 21%-49%, and ultrasound rates ranged from 2%-26%.

CT has been promoted as a method to improve diagnostic accuracy in patients with acute abdominal pain. In a landmark 1997 study, Rao et al demonstrated that CT lowered negative appendectomy rates in adult patients with acute abdominal pain. Subsequently, Garcia Peña et al found CT to be highly accurate for identifying or ruling out appendicitis in pediatric patients with equivocal presentations. Following these publications, a widespread increase in abdominal CT use was observed. In some adult cohorts, increased CT use was associated with reductions in negative appendectomies. Similar decreases in pediatric populations have not occurred. In addition, increased CT use has not affected rates of appendiceal perforation in children or adults. Thus, the benefits of CT for patients with equivocal

presentations have not been generalizable to larger cohorts of children with acute abdominal pain.

Overuse of CT is problematic given the risks of radiation exposure and increased costs of care. As a result of their smaller size and increased organ sensitivity, pediatric patients are especially vulnerable to radiation-induced injuries. Researchers estimate that 1 radiation-induced malignancy may result from every 700 pediatric abdominal CT scans obtained in young males, and the risks may be even higher in young females. This is especially troubling given the rapid increase in CT use nationwide. Furthermore, for children who meet obvious clinical criteria for appendicitis, CT may delay operative care and increase costs. For pediatric patients with low likelihood of appendicitis based on history and clinical exam, CT may prolong ED length of stay and increase costs. Although CT has a demonstrated sensitivity of 94% (95% CI 92%-97%) and specificity of 95% (95% CI 94%-97%) for identifying appendicitis in children, its positive predictive value decreases substantially when used in children with low likelihood of appendicitis. For a subset of pediatric patients with acute abdominal pain, the risks of CT may outweigh the benefits.

General or non-pediatric facilities are the ideal clinical setting to implement interventions for reducing CT use. In the United States, most emergent care for children is provided in general EDs. Only 7% of hospitals in the United States have EDs exclusively dedicated to pediatric care. Recent data from the National Hospital Ambulatory Care Survey demonstrate that children with abdominal pain receiving care at general facilities were more likely than those at children's hospitals to undergo CT. Plausible explanations for this difference include 1) general ED providers may have less confidence than pediatric ED providers in eliciting and interpreting physical exam findings in children and 2) general ED providers may be more familiar with adult guidelines that advocate CT to diagnose appendicitis. Children undergoing CT at general institutions are also at risk of receiving a radiation dose that is excessive for their height and weight.

Protocols to reduce reliance on abdominal CT in children have been safely developed and implemented in pediatric and general emergency departments. In 2004, Garcia Peña and colleagues demonstrated the theoretical benefits of an appendicitis decision rule that first stratified patients based on their white blood cell count (WBC) and then applied a selective imaging protocol, with ultrasound as the first-line imaging. Similarly, utilizing data from 10 pediatric EDs, our group has derived and validated a decision rule to identify patients at low risk of appendicitis using recursive partitioning. We found that the absolute neutrophil count (ANC) was the first node, or the most powerful tool, for identifying pediatric patients with acute abdominal pain who could forgo diagnostic imaging. Additional key predictors were: focal right-sided pain, pain with walking, emesis, and duration of pain. Several other pediatric and general EDs have implemented protocols that risk-stratify based on WBC and additional clinical variables. Although there are no national guidelines regarding the management of children with acute abdominal pain, there is an increasing consensus among surgeons and ED providers on the use of risk stratification and the need to limit unnecessary CT exposure. Collectively, single-site studies have documented that it is possible to safely reduce rates of advanced diagnostic imaging in patients with suspected appendicitis. To date, point-of-care appendicitis protocols that integrate laboratory data, symptoms, and clinical history have not been implemented and evaluated in multisite studies, likely due to logistical and practical barriers.

EHR-linked, Web-based CDS is a scalable model that has successfully changed clinician behavior and improved quality of care in a range of settings. Many CDS studies have been single-site efforts performed in academic medical centers. A systematic review of research studies conducted through 2004

included 100 randomized and nonrandomized trials with concurrent controls, compared computer-based CDS with routine care. The authors noted that computer-based CDS improved clinician performance in 64% of the studies. Two of four ED-based trials showed that CDS led to improvements in diagnosis. In all clinical settings, improvement was noted more often with automatic delivery of CDS versus when users had to activate the CDS. These results mirror our previous work demonstrating that CDS in outpatient clinics improves clinician adherence to diabetes guidelines and glucose and blood pressure control in diabetic patients. In our previous work, we found that ED physicians are receptive to CDS based on validated prediction rules and are open to multiple means of incorporating CDS into the EHR.

Implementing CDS via the EHR in multiple EDs presents unique challenges. EDs provide care to a high volume of acutely ill patients requiring rapid management decisions despite often incomplete clinical information. The proposed CDS will gather information from multiple sources at multiple times during the patient encounter, integrate these data using previously validated clinical decision rules, and provide evidence-based patient-specific clinical care recommendations in real time. Furthermore, ED clinicians work in dynamic and complex systems; each ED has evolved a particular method of decision-making or clinical workflow. For CDS to be successful, it is necessary to assess and account for local ED processes and clinician perceptions. Given the current variability in ED management of pediatric patients with acute abdominal pain, local consensus for key recommendations in Appy-CDS is imperative. As in our previous work, we will conduct detailed workflow analysis, obtain key stakeholder feedback, seek endorsement from clinical leaders, and conduct pilot testing and iterative refinement of our CDS system. Ultimately, the success of Appy-CDS will depend on its ability to save time, to provide accurate clinical care recommendations that augment clinician judgment, and to promote appropriate utilization of diagnostic imaging.

CDS integrated into an existing EHR platform and delivered at the point of care is the ideal scalable intervention for reducing unnecessary CT use in children with acute abdominal pain. In their 2007 article on US EDs, Gausche-Hill et al wrote, “Key opportunities for improving pediatric emergency care lie in non-children’s hospitals, where the vast majority of care occurs”. The Appy-CDS intervention integrates clinical information to optimize management of children with acute abdominal pain in general EDs. Moreover, our technical approach is a useful template to generalize ED point-of-care CDS to a range of clinical conditions.

### c) Innovation

The potential for computerized CDS to improve practitioner performance and adherence to guidelines is widely recognized. However, the impact of EHR-linked CDS on patient outcomes has been variable. Review of previous negative studies identifies 3 principal reasons for failure: (a) Clinicians have not accessed the CDS information in a timely fashion, (b) the CDS has been limited to simple prompts or reminders, and (c) the CDS has not provided personalized information. This project addresses these limitations by moving beyond simple computer prompts and reminders to provide more sophisticated, patient-specific recommendations. Furthermore, the CDS is integrated in the EHR at multiple points during the encounter, ensuring maximum visibility and allowing for varying practice styles and workflows in disparate EDs.

Previous CDS for pediatric emergency care have primarily been developed and implemented in academic children’s hospitals. Because most pediatric ED visits and radiation exposures are in general EDs, there is an urgent need to study the effectiveness of pediatric-specific CDS in these settings. We propose

to work closely with site-based leadership to develop and implement the Appy-CDS system in 2 large health systems with 14 general EDs. The EDs in this study vary in pediatric patient volume and geographic region. Thus, our intervention will be relevant to and more broadly generalizable to the settings in which most pediatric patients receive emergent care in the United States.

The use of a Web service to host the CDS algorithms is a design feature that maximizes the scalability of the intervention, facilitates updating of algorithms as evidence or clinical practice changes, and maximizes the impact of CDS resources to improve quality of care for pediatric patients with acute abdominal pain. For instance, although magnetic resonance imaging (MRI) is currently not a standard diagnostic tool for pediatric patients with acute abdominal pain, our protocols could be modified to address use of this imaging modality in the future.

**Innovation in Assigning Patients a Personalized Risk of Appendicitis:** This project builds on previous successful efforts by our team in developing and implementing CDS to support goal-based guidelines. Previous CDS interventions for acute abdominal pain have largely presented clinicians with overarching, general evaluation options rather than patient-specific guidance. A personalized risk assessment is more likely than a general recommendation to substantially change practice patterns. The Appy-CDS will use available clinical data to estimate a quantifiable and patient-specific risk for appendicitis and prioritize the potential benefits of additional imaging modalities. Successful adoption of the proposed CDS for acute abdominal pain will facilitate development of additional CDS tools to enhance the care of children and adolescents in the ED.

An important aim of this study is to promote the appropriate use of diagnostic imaging. Due to variability in ultrasound performance, protocols that simply recommend ultrasound for all patients with acute abdominal pain may have unintended consequences and ultimately increase total imaging rates. To avoid this, the Appy-CDS tool will provide detailed recommendations for when diagnostic imaging is not required as well as guidance on when CT may be more appropriate than ultrasound. By providing nuanced, evidence-based recommendations, Appy-CDS will offer guidance tailored to each patient.

#### d) Preliminary Studies

**Pilot data:** We recently completed a single-center pilot study to implement CDS integrated in an EHR for pediatric patients with acute abdominal pain. For this project, based in the 2 primary EDs of Children's Hospitals and Clinics of Minnesota (Children's Hospital), we engaged a multidisciplinary team of radiologists, surgeons, and ED physicians to develop a consensus care pathway. Similar to the current proposal, goals of the pilot were to reduce CT use among pediatric patients with ED visits for acute abdominal pain. The pilot CDS stratified patients into 3 risk groups based on previously validated decision rules. First, we identified pediatric patients with acute abdominal pain at low risk for appendicitis who could safely forgo CT by applying our previously derived and validated decision rule. Patients with an ANC  $<6.75 \times 10^3/\mu\text{L}$ , absence of nausea, and absence of maximal tenderness in the right lower quadrant were identified as at low risk for appendicitis. Second, to determine which patients were at high risk for appendicitis and could proceed to the operating room without imaging, we used the externally validated Pediatric Appendicitis Score (PAS). The remaining patients were classified as medium risk, and ultrasound was the recommended initial imaging modality. We then worked with our informatics group to create a simple "time-of-ordering alert": the pilot CDS tool was presented to clinicians when ordering a CT or ultrasound for patients with acute abdominal pain. The CDS tool was modified and refined in two phases. Drs. [name] and [name], members of the Clinical Advisory Council for the current proposal, were instrumental to the success of the pilot.

Over the 36-month study period, 4,234 pediatric and adolescent patients with acute abdominal pain received care in the pilot EDs. Of these, 778 (18%) had appendicitis and 178 (23% of appendicitis cases) had a perforated appendix. After CDS was implemented, 942 (22%) had an abdominal CT, and 1,666 (39%) had an ultrasound. Interrupted time series design revealed a significant 23% decline in CT use post-implementation ( $OR=0.77$  (95%CI.67-.88)  $P<0.01$ ) (Figure 1). Safety outcomes remained unchanged over the study period.

The pilot study provided information critical to the design of this project. Although the pilot reduced CT use, total imaging (CT or ultrasound) did not decrease. In addition, after a marked early post-implementation decrease in CT, further reductions were limited despite the Phase II refinements. Review of the intervention revealed 3 key themes we will address in the current proposal: a) clinicians prefer patient specific information to general approaches to acute abdominal pain b) clinicians do not want to calculate a patient's risk for appendicitis by entering multiple data points, and c) a "time-of-ordering alert" can promote replacement of CT with ultrasound but is not sufficient to reduce total diagnostic imaging. Based on the pilot data and our team's previous work, we conclude that the success of the proposed Appy-CDS intervention can be maximized by: (1) Making decision support available at the point of care and based on all available relevant clinical data; (2) Providing patient-specific information in a sophisticated manner, beyond simple prompts or reminders; (3) Integrating the CDS into the routine flow of patient care; and (4) Ensuring adequate ED staff training, process measurement, and feedback to reinforce use.

**Figure 1. CT, US and Total Imaging Rates of Patients with Possible Appendicitis**

[figure not shown]

### 3) Study Sites and Population

We will conduct a prospective cluster-randomized clinical trial at 17 general EDs in two large care systems to evaluate the impact of Appy-CDS on CT and ultrasound use, health care outcomes, and direct medical expenditures. We will first measure ultrasound and CT use for 6 months pre-intervention in children identified at triage as at risk for appendicitis presenting for care in a participating ED. We will then group some sites with significant provider cross-coverage and pair within clusters by pediatric volume. We will then randomize half of the clusters to receive the full Appy-CDS. CT and ultrasound utilization in intervention and control sites will be measured for 24 months after the full Appy-CDS “go-live” date. Rates of perforation, negative appendectomies, and missed appendicitis will be monitored as safety outcomes. We will compare resource use and re-visit rates between intervention and control EDs within 7 days of the index ED visit. Figure 2 is an overview of the study design.

This study includes 17 general EDs operated by two health systems: HPMG (Regions, Hudson, Lakeview, Methodist, Westfield and Amery), in the Upper Midwest and KPNC (Sacramento, Roseville, South San Francisco, San Rafael, Santa Clara, South Sacramento, San Leandro, San Francisco, Fremont, Oakland and Richmond). These 17 EDs provide care to a diverse pediatric patient population (34% Hispanic, 19% African-American, and 11% Asian). None of the participating EDs are university-based; however, 5 EDs have academic affiliations. Most ED clinicians are board-eligible or board-certified emergency medicine physicians. Ultrasound is available at each participating ED, and 5 sites are referral centers for pediatric appendectomies. Each ED currently uses the EpiCare EHR (Verona, WI). Both health systems have agreed to participate and work with the study investigators to create linkages between their EHR and the Appy-CDS tool. Collectively, the 17 participating EDs have more than 650,000 annual ED visits, of which 101,014 are patients aged 5-20 years).

To be included, patients must: a) be 5-20.9 years old on the index date, and b) present to a participating ED with a chief complaint of acute abdominal pain.

#### a) Exclusion Criteria

Using data from the EHR and gathered from triage-based prompts introduced at all participating EDs, we will identify patients with a current pregnancy, previous abdominal surgery, trauma, cystic fibrosis, sickle cell anemia, inflammatory bowel disease, or other selected comorbidities at the prime site, or with an ED visit for abdominal pain in the prior 7 days. These patients will be excluded from the study cohort. As described below, based on responses to the initial screening questions, patients with >120 hours of abdominal pain or patients with no right sided or generalized abdominal pain will also be excluded from the risk score calculation and further analyses.

If patients are transferred to an outside facility (outside of KPNC or HealthPartners networks) for surgery *and* we are unable to review their operative and pathology notes, they will be excluded from the safety analyses. These patients will be retained in the primary analyses, evaluating the use of CT or US, with the diagnosis of appendicitis or not appendicitis assigned based on provider impression and imaging available at the time of ED discharge / transfer.

#### b) Patient Recruitment

Patients will be identified based on a chief complaint of abdominal pain and at HP, using automated alerts within the electronic health record (EHR). A flag will be created for patients who meet eligibility criteria. The flag will be stored in Epic for use by the full clinical decision support (CDS) at a later point. Although

the process of identifying eligible patients is fully automated, success of the study depends, to a large extent, on the engagement of nursing staff and providers at all participating sites. Enrollment can be maximized by using a combination of the methods outlined below.

1. Education of nurses, physicians and residents providing care in each emergency department (ED).
  - a. Present the study at ED staff meetings.
  - b. Train nurses and providers at shift meetings or other meetings as appropriate.
  - c. Use the “train the trainer” approach including the recruitment of “champions” to promote the project.
2. Put in place a system to remind physicians about the EHR tools available to them.
3. Post laminated cards with project info next to all workstations as reminders to staff regarding the purpose and importance of responding to the EHR alerts.
4. Incentives to nurses or providers for completing the EHR-linked tools.
5. Provide feedback to nurses and providers regarding use rates.

## 4) Allocation of Interventions

EDs will be stratified by hospital system and then pair-matched based on pediatric patient volume. Matching EDs on selected characteristics *a priori* minimizes possible sources of bias by balancing potential ED-level confounders between intervention arms. It will sharpen our comparisons of interest and it is recommended for trials with a small number of clusters Further, this design allows staggered implementation without breaking concealment to better control for seasonal variation in ED use. Matched EDs will be randomly assigned, in pairs, to one of the two arms using a block design. The randomization scheme will be prepared by the study statistician ([name]) using a computerized random-number generator. Assignment will be revealed before implementation. Emergency Department stakeholders at each site have agreed to randomization before initiation of the study.

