To test the effectiveness of the full Appy-CDS system, we will compare ratios of CT and ultrasound use pre and post implementation across study arms (i.e., difference-in-differences approach). This is best described as estimating a time (pre/post intervention) by treatment interaction. We will conclude that the Appy-CDS changed CT or other imaging and/or ultrasound utilization if significance at the 5% level is found using a 2-tailed test. To best estimate this effect across the entire pediatric ED patient population, we will fit a marginal model that provides population-level impacts averaged across all clusters. To do this, generalized estimating equations (GEE) and a log-linear model with an autoregressive covariance structure will be employed. A parsimonious approach to multivariable adjustment will be followed, and only factors found unbalanced across study arms at the 5% level and associated with the effect size (>.2) will be retained and included in the models as covariates.

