### Exploratory Analysis

Effectiveness of the intervention may vary by population subgroup and provider. Although our study may be underpowered to detect such differences, we intend to conduct two exploratory analyses. The first will examine if patient and provider characteristics act as moderators of the overall intervention effect, examining both single predictors, such as patient age, sex, and risk of appendicitis and a composite moderator. Our second exploratory analysis will focus on the process of provider change, comparing trajectories of imaging and ultrasound use across intervention sites.

**Hypothesis 4 – resource utilization:** The skewed nature of health care utilization patterns is well known. This is particularly true of episodic hospital data such as the treatment of appendicitis which

has a known likelihood of complications. We will follow the standard outlined in the literature and model the total amount of emergency and hospital-based care used during the treatment episode and the likelihood of re-visits due to misdiagnosis or surgical complications. This will begin by modeling the likelihood of re-visits due to an adverse event (e.g., wound infection, abdominal abscess, and obstruction) or other unplanned re-admission using logistic regression. Then we will directly model the total costs of the treatment episode. The choice of a statistical approach to model episode costs will depend on the observed distribution of these costs. The most common approach is the log-linear model. However, this model requires the use of a retransformation factor that is sensitive to heteroscedasticity. Thus, we will explore the use of other specifications such as the gamma distribution and compare alternatives using a modified Hosmer-Lemeshow test. To facilitate this approach, an alternative hierarchical estimation technique, GEE, may be considered. GEE extends the generalized linear model to allow for covariance matrices that specify clustering of the data (e.g. at the ED level).

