**List of variables for Hypothesis 2 analysis.**

| Variable Name    | Variable Type and Length (bytes) | Values                                                                                                                                                                                                                                                                                                                   | Variable description         |
|------------------|----------------------------------|--------------------------------------------------------------------------------------------------------------------------------------------------------------------------------------------------------------------------------------------------------------------------------------------------------------------------|------------------------------|
| Study_ID         | char(7)                          | HP00001, HP00002, etc
KP00001, KP00002, etc                                                                                                                                                                                                                                                                           | Study id                     |
| Site             | num(8)                           | 101=Regions,
102=Lakeview,
103=Westfield,
104=Hudson,
105=Methodist,
106=Amery
201=Sacramento,
202=Roseville,
203=South San Francisco,
204=San Rafael,
205=Santa Clara,
206=South Sacramento,
207=San Leandro,
208=Fremont,
209=Oakland,
210=Richmond,
211=San Francisco | Site of Emergency Department |
| Intervention_arm |                                  |                                                                                                                                                                                                                                                                                                                          |                              |

|                  |          |                                                                                                                                                                                                               |                                                                         |

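### The randomised and analysed unit is not consistently defined: provider-sharing groups of EDs in one section, single EDs in another, and no group or pair code in the variable lists

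*Combined protocol and SAP*

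**What the plan says.** Section 3 (Study Sites and Population) sets out the sequence: "We will then group some sites with significant provider cross-coverage and pair within clusters by pediatric volume", then "We will then randomize half of the clusters to receive the full Appy-CDS". The unit randomised there is a cluster that may hold several EDs. The phrase about pairing is itself unclear: taken literally it pairs EDs inside a cluster, while the next sentence randomises clusters whole.

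Section 4 (Allocation of Interventions) does not mention grouping. It stratifies EDs by system, matches them on volume, and states: "Matched EDs will be randomly assigned, in pairs, to one of the two arms using a block design".

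Section 6, Hypotheses 2 and 3, will "fit a marginal model that provides population-level impacts averaged across all clusters" by GEE, without saying what a cluster is. The Hypothesis 4 text says a GEE may be considered and describes "covariance matrices that specify clustering of the data (e.g. at the ED level". That is the only place where a clustering level is named for a GEE. Sample size and power works with 14 sites and patients per ED.

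The enrolment report in section 7 and Table 7 in section 9 are organised by cluster. Table 7, labelled an example, shows 2 + 2 clusters at HealthPartners and 4 + 4 at Kaiser Permanente, 12 in all, from 6 + 11 = 17 EDs.

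In Appendix E, the Hypothesis 1 and 2 lists hold an arm field and a 17-value site code, described as "Site of Emergency Department", but no cluster or pair code. The Hypothesis 4 list has no site, cluster or arm field.

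**The concern.** EDs grouped because they share clinicians always fall in the same arm and may change their imaging practice together. If each is entered as its own independent unit, the variance of the arm comparison is too small. A change made by one shared clinical team could then count as two or three independent confirmations.

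What is at stake is the 5% error rate for CT use, total imaging and resource use. An analyst holding only these documents could not reconstruct the randomised groups: no section says which EDs are grouped, and the file layout does not carry the grouping. The readily available choice would be the site code.

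**Working it through.** **The plan's own figure.** Table 1 gives power for 14 sites, ICC 0.05, baseline CT rate 0.30 and 200/300/400 patients per ED per year: 80/91/98% for a 25% decrease and 63/82/86% for a 20% decrease.

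- The ordinary cluster formula (7 EDs per arm, design effect 1 + (m - 1) x 0.05) gives only 19-29%.
- A pre/post difference-in-differences over 6 and 24 months, with each ED's effect perfectly stable over time, gives 81/94/98% and 62/79/89%. Three of six cells are within 2 points.

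Table 1 is thus not exactly reproduced. It appears to rest on a temporal correlation that the plan mentions without giving a value, so the mismatch is no evidence of error. It does show that Table 1 counts sites, not randomised groups.

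**Analytic check.** Suppose 17 EDs in 12 groups are counted as 17 independent units, and rho is the within-group correlation of the EDs' pre/post changes. Then

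DE = 1 + rho x (sum of m² / sum of m - 1), and actual alpha = 2 x (1 - Phi(1.96 / sqrt(DE))).

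For five groups of two and seven single EDs, sum of m² = 5 x 4 + 7 = 27, and 27/17 - 1 = 0.588. At rho = 0.5, DE = 1.294 and alpha = 8.5%. At rho = 1, DE = 1.588 and alpha = 12.0%.

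| Assumed layout | rho 0 | 0.2 | 0.5 | 1 |
|---|---|---|---|---|
| Five groups of 2 | 5.0% | 6.4% | 8.5% | 12.0% |
| Groups of 3, 2, 2, 2 | 5.0% | 6.7% | 9.2% | 13.4% |
| Groups of 4 and 3 | 5.0% | 7.5% | 11.3% | 17.2% |

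**Simulation with t inference, no true effect.** Inputs: ICC 0.05; 112 pre and 333 post patients per ED (Table 7 totals 1,899 and 5,668, each divided by 17); randomisation of 2 of 4 HealthPartners and 4 of 8 Kaiser Permanente groups; three assumed layouts; 20,000 replicates. The comparison is a t-test on 17 ED changes (15 df) against one on 12 group means (10 df). Columns give the part of the ICC that is period-specific.

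| Shared within a group | 10% | 20% | 50% |
|---|---|---|---|
| Half, ED as unit | 6-7% | 7-8% | 8-9% |
| All, ED as unit | 8-9% | 10-11% | 11-13% |

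With the group as unit the rate is about 5%. With no period-specific part, the ED-level test is also at about 5%. A post-only comparison, if one were used for Hypothesis 4, gives 8-9% (half shared) and 13-15% (all shared).

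**Second simulation.** Inputs: 300 patients per ED per year, 6 months pre and 24 months post, 20% or 50% of the ICC period-specific, 4,000 runs per scenario, Monte Carlo error about 0.3-0.6 points.

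- t-test on 17 EDs: 5.0-5.6% with no sharing, 5.6-7.1% with 20% shared, 7.4-9.3% with half, 10.4-15.0% with all.
- t-test on 12 clusters: 4.3-5.6% throughout.
- Log-link GEE with ED-level sandwich errors and a normal reference: already 8.2-9.3% with no sharing.
- The same GEE with cluster-level sandwich errors: 10.6-15.1% with a normal reference, 6.6-10.9% with t on 10 df.

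The GEE runs used an independence working structure in place of the planned autoregressive one.

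**The case against.** The best defence is that the plan never commits to an ED-level analysis. For CT and imaging it speaks of clusters, and sections 3, 7 and 9 use that word for the randomised or reported unit, so the natural reading is the randomised group. The ED level appears once, as an example, for a cost model that may not be used. Section 4 can be read together with section 3, with grouping done first. Appendix E is a data dictionary and visibly unfinished: the arm field has no values, and there is no pre/post or go-live field, although the model needs one. The section 7 report sets sites beside clusters, so a mapping is evidently meant to exist. Finally, much of the error inflation under a plain GEE comes from the small number of units, whatever the unit is.

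Most of this stands, and it limits the claim. A reader might infer that the plan specifies the ED as the unit for all outcomes; the text does not support that. Nor does a missing field prove an intention to analyse by site. A reader might also infer that section 4 would send EDs with shared clinicians to opposite arms; that follows only if section 3 is ignored.

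What remains is that section 4, the section governing allocation, describes a different unit from section 3, the term cluster is undefined where inference depends on it, and no mapping is given. The small-sample problem is additional: the ED-level excess in the t-test comparisons comes from the unit alone.

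**Conclusion.** The point holds as an inconsistency in the randomised unit and an undefined unit of analysis. If grouped EDs were analysed as independent, the false-positive rate with t inference would be about 5% when they share no period-specific change or ED effects are stable over time, about 6-9% when half is shared, and about 8-13%, up to about 15% in some layouts, when all is shared.

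It is tempting to quote 8-13% as the error rate of the planned analysis. The documents do not support that: the range needs full sharing, whereas section 3 says only that cross-coverage is significant at some sites. Neither the degree of sharing nor the group sizes are given, and the count of 12 clusters comes from an example table.

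It is also tempting to think that moving the GEE to the 12 clusters restores 5%. It does not: a plain sandwich GEE on 12 clusters stayed liberal even with a t reference.

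**What to change.** 1. Reconcile sections 3 and 4 so that both name the provider-sharing group of EDs (a single ED where there is no sharing) as the unit that is paired and randomised, and reword the pairing phrase in section 3.
2. List which EDs form each cluster and which clusters form each pair. Add Cluster_ID and Pair_ID to the analysis files for Hypotheses 1, 2 and 4.
3. State for Hypotheses 2 to 4 that inference is at the level of the randomised cluster, and replace the ED-level example in the Hypothesis 4 text.
4. Specify a small-sample-valid method: a cluster-level t-test on pre/post changes, a permutation test over the actual randomisation, or a GEE with bias-corrected standard errors and cluster-based degrees of freedom. Of these, only the cluster-level t-test was checked here, and it held about 5%.

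The clerical cost is two variables and a few sentences. The statistical cost is real. Standard errors grow by about sqrt(DE): for the first two layouts, 1.14-1.16 at rho 0.5 and 1.26-1.31 at rho 1, so roughly 10-30% if sharing is substantial, and about 43% for groups of 4 and 3 with full sharing (sqrt(2.059)). The critical value also moves from 2.131 (15 df) to 2.228 (10 df). Power stated on 14 sites would be less favourable and should be restated for the randomised clusters.
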